#### Outcome Measures

Based on results of previous studies [27,28], the primary outcome measures will be

(i) lead limb post obstacle distance,

(ii) lead and trail limb clearance,

(iii) step length after clearing the obstacle,

(iv) anterior-posterior (AP) separation between the centre of mass (COM), COP and heel of the stance limb during lead limb clearance, and

(v) instantaneous COM velocity at lead limb clearance.

#### Statistical Analysis

Data will be compared with normative data using multivariate analysis of variance. Adjustment will be made for any covariates which may impact on obstacle crossing, such as leg length. Performance on the primary gait measures will be compared between participants in the experimental and control groups of the randomised controlled trial, using multivariate analysis of variance, with adjustment for covariates identified as differing between the two groups at this measurement occasion.

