If a reduction in falls is observed, it is important to understand the mechanisms by which this has occurred. The reduction in falls may be secondary to an improvement in stability, or it may reflect increased caution when performing activities such as walking. The impact of the intervention on stability during walking is particularly pertinent, as the control of balance while walking is complex due to the inherent instability and dynamic nature of the task [26]. Examination of stability during walking will provide insight into the mechanisms by which the intervention may have an effect on reducing falls. Obstacle crossing has been shown to be a useful paradigm for exploring stability in walking following stroke [27,28].

The aims of this study are therefore threefold:

(i) to evaluate the effectiveness of a multi-factorial falls prevention program for stroke survivors returning home after rehabilitation,

(ii) to examine the temporal relationship between fear of falling, falls and function in the above population, and

(iii) to evaluate the contribution of gait impairments to the task of obstacle crossing in the context of a falls prevention program.

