#### Randomisation

Participants will be assessed for eligibility, provided with information about the study, provide informed consent, be enrolled into the study and complete the baseline assessment prior to allocation into the control or intervention group. Participants will be assigned to the control or intervention arm of the study according to a computer generated random allocation sequence concealed from the researchers in opaque envelopes. Staff not involved in the study will undertake the sequence and concealment. The envelopes containing the allocation will be stored in one location and participants will be assigned in order of completed baseline assessment.

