#### Intervention

The intervention consists of a multi-factorial falls prevention program implemented by a physiotherapist including:

1) an individualised home exercise program with strength, balance and walking components based on the Otago Exercise Programme [45,46]. Exercise selection and dosage will be determined by the research physiotherapist and administered in the participant's home at a visit following the baseline assessment. Exercises will be selected to address balance and mobility problems identified in the baseline assessment and will be tailored to the level of each participant. The program will be monitored and modified by the physiotherapist at two subsequent home visits during the 12 month study period. Participants will be advised to undertake the exercise program at least five times per week. Participants will be provided with an exercise recording sheet to indicate completed exercises, and adherence to the exercise program will be assessed by the physiotherapist at the review visits.

2) falls risk minimisation strategies based on the falls risk factors identified in the baseline assessment in the context of falls prevention activities already in place, together with participant preference. Falls risk factors will be identified using the FROP-Com, which is designed to identify the level of falls risk associated with the common falls risk factors in community-dwelling older persons. Interventions may include, for example, referral for vision assessment and correction, changes to footwear, change in walking aid, referral for home modifications, medication review, and continence review and management. Guidelines for this component of the intervention are summarised in Table 1.

**Table 1 T1:** Guidelines for intervention options for FLASSH study: falls risk minimisation

**Risk factor**	**Intervention options if risk factor identified**
History of falls/falls injuries	Referral to GP Appropriate acute management if injury recent
Medications (number)	Refer to GP for medication review
Medications (associated with increased falls risk)	Refer to GP/specialist for medication review
Medical conditions (associated with increased falls risk)	Refer to GP/specialist for review
Sensory loss: vision	Brochure on lighting and home safety Refer to optometrist Refer to Ophthalmologist via GP Refer to Vision Australia (includes mobility training and aids for visually impaired) Refer to OT for home assessment Refer to GP

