### Obstacle Crossing Sub-Study

Participants recruited in the primary study from both intervention and control groups through Melbourne sites will be approached to participate in an additional measurement session at twelve months following enrolment in the study. It is anticipated that 30 subjects will be recruited for this sub-study.

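### Obstacle-crossing sub-study: adjusting the arm comparison for covariates that differ at 12 months can remove part or all of the intervention's effect on gait stability

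*Protocol article*

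**What the plan says.** The Statistical Analysis section of the Obstacle Crossing Sub-Study describes two comparisons.

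- **Patients against normative data.** The covariate sentence that follows reads "Adjustment will be made for any covariates which may impact on obstacle crossing, such as leg length".
- **Arm against arm.** The primary gait measures are "compared between participants in the experimental and control groups of the randomised controlled trial, using multivariate analysis of variance". The rule for choosing covariates in this second comparison is given as "with adjustment for covariates identified as differing between the two groups at this measurement occasion".

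The opening of the sub-study fixes the occasion: participants are invited to "an additional measurement session at twelve months following enrolment in the study". On size it says "It is anticipated that 30 subjects will be recruited for this sub-study", with no power calculation.

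Three other sections bear on the point. The Intervention section describes "an individualised home exercise program with strength, balance and walking components". The Background gives the purpose: "Examination of stability during walking will provide insight into the mechanisms by which the intervention may have an effect on reducing falls". The Randomisation section says that participants "complete the baseline assessment prior to allocation into the control or intervention group".

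**The concern.** The covariates are to be picked because the arms differ on them at a session held a year after enrolment. By then the arms may differ because the programme worked. The Outcomes section lists chair-stand strength, gait velocity, Step Test, Timed Up and Go and activity as secondary outcomes at follow-up, so the trial itself treats these as things the intervention may change. Under the stated rule they become candidates for adjustment exactly when it has changed them.

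Adjusting for a variable on the path from treatment to outcome takes out the part of the effect that runs through it. One of the sub-study's primary measures is centre-of-mass velocity at lead limb clearance. Adjusting that for 12-month walking speed would come close to adjusting an outcome for itself.

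At stake is the question raised in the Background: would fewer falls reflect better stability, or only more caution? An estimate of the stability effect that is biased towards zero would tilt the answer towards caution. The rule also leaves the model to be settled by the observed 12-month data rather than in advance.

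**Working it through.** **What the text permits.** The between-arm clause does not limit covariates to baseline or fixed characteristics. Leg length is given as an example only in the sentence after the normative comparison. Nothing in the article presents the adjusted result as a mediation or direct-effect analysis.

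**There is no figure to reproduce.** The article attaches no effect size, SD or power to this comparison. What follows is an illustration.

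**Inputs.** From the article: about 30 participants and a 12-month session. Assumed: an even split of 15 per arm; five candidate 12-month covariates, of which one (M) responds to treatment and four are noise; selection when the arms differ at p<0.05; and the values of a, b and d below.

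**Model.** With T = 0 or 1 for arm:

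- M = a·T + e, with e of SD 1
- Y = b·M + d·T + error, with error SD √(1 − b²), so Y has within-arm SD 1
- true total effect = a·b + d; adjusting for M leaves d

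True totals: 0.8 × 0.6 + 0 = 0.48; 1.2 × 0.6 + 0 = 0.72; 0.8 × 0.6 + 0.3 = 0.78; 0.8 × 0.3 + 0.3 = 0.54.

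**Results** (4,000 simulated sub-studies per row; the Monte Carlo error of an unadjusted mean is about √(2/15)/√4000 = 0.006 SD):

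| a | b | d | True total | Unadjusted mean | Mean under the rule | Rejection, unadjusted to rule | M selected |
|---|---|---|---|---|---|---|---|
| 0.8 | 0.6 | 0 | 0.48 | 0.48 | 0.13 | 25% to 7% | 56% |
| 1.2 | 0.6 | 0 | 0.72 | 0.72 | 0.04 | 48% to 5% | 89% |
| 0.8 | 0.6 | 0.3 | 0.78 | 0.77 | 0.43 | 53% to 22% | 55% |
| 0.8 | 0.3 | 0.3 | 0.54 | 0.54 | 0.36 | 29% to 15% | 57% |
| 0 | 0.6 | 0 | 0 | 0.00 | 0.00 | 5% to 4% | 5% |

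**Reading the table.**

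1. The more the programme changes M, the more often M is selected: 56% of runs at a = 0.8 and 89% at a = 1.2.
2. The bias is larger than the selection frequency alone implies. In row 1, if unselected runs kept the full effect, the mean would be (1 − 0.563) × 0.48 = 0.21. It is 0.13, because M escapes selection mainly when its difference happens to be small, and the outcome difference is then small too.
3. With a direct effect, part of the estimate survives (rows 3 and 4).
4. If treatment does not move the covariate, the rule causes no bias (last row).

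**The case against.** Four arguments deserve a fair hearing.

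**The covariates may be harmless.** The section's only named covariate is leg length, which treatment cannot change, and the clause might mean imbalance in background traits among those who attend. If only such traits were selected, no treatment effect would be removed. This stands as a limit: a reader might infer that the plan is certain to adjust the effect away, and the article does not support that, since it names no 12-month gait, strength or activity covariate for this model. But nothing excludes them either, and even the benign reading leaves selection by observed imbalance.

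**Thirty volunteers at 12 months may well be imbalanced.** True. That is a reason to adjust for pre-specified baseline or fixed characteristics. It is no reason to adjust for differences that have arisen since allocation.

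**The comparison is weak anyway.** With 15 per arm, the unadjusted analysis in row 1 rejects only 25% of the time, so a real 0.48 SD effect is usually missed regardless. A reader might infer that the clause alone turns a detectable benefit into a null result; at this sample size that is too strong. The bias in the estimate remains. The illustration also uses a single outcome, whereas the plan is multivariate.

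**The stated aim is a different one.** A reader might infer that aim (iii) is defeated. As worded, it concerns how gait impairments contribute to crossing obstacles in the setting of a falls programme, and the normative comparison serves it without using this clause. The link to the intervention's mechanism comes from the Background discussion.

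Deferring the covariate list to an analysis plan would not be enough, because the article already states the rule by which the list is drawn up.

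**Conclusion.** The clause is wrong as written. It selects covariates by their difference between randomised arms after the intervention, so it can remove part or all of the effect being estimated. The size is conditional: total loss if the effect runs wholly through the selected covariates, partial loss otherwise, and none for traits that treatment cannot change. Under the assumed values the mean estimate drops from 0.48 to about 0.13 SD with full mediation, and from 0.77 to 0.43 SD with a 0.3 SD direct effect. These figures rest on the assumed even split, covariate shift, slope and p<0.05 rule, none of which the article gives.

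Severity is moderate. The damage is to the Background's purpose of learning whether the intervention acts through stability. Aim (iii) as worded, the normative comparison and the primary falls outcome with its negative binomial analysis are not affected.

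**What to change.** Replace the adjustment clause for the arm comparison with a short list of covariates, fixed before the 12-month data are examined, that treatment cannot modify:

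- measures already taken before allocation, for example baseline comfortable gait velocity and baseline Step Test;
- fixed traits such as leg length, whenever measured. Leg length is not in the listed baseline battery, so the criterion should be whether treatment can change the variable, not the date of measurement.

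State that treatment-modifiable variables measured at 12 months will not be adjusted for in this comparison. Report the arm comparison as exploratory, since its roughly 30 participants volunteer after randomisation.

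The cost is one sentence and two or three degrees of freedom: with 30 participants in two arms, the error degrees of freedom go from 30 − 2 = 28 to 26 or 25. No new trial assessments are needed.

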## Discussion

Despite evidence of the effectiveness of falls prevention activities for community-dwelling older people, the applicability of these interventions has not, to date, been evaluated in community-dwelling stroke survivors. Interventions related to falls risk factors, for example, strength and balance training, have been shown to be effective in the stroke population in achieving improved physical performance, but the impact on falls has not always been reported. This study aims to address this gap as well as providing further insights into how fall-related self-efficacy changes over time, and the contribution of gait impairments to stability when negotiating obstacles. If the study shows that the intervention is effective in reducing falls, the results will provide a sound basis for broad implementation of a falls prevention program that could be commenced prior to discharge from hospital with relatively little additional resources required. Successful outcomes from the studies have the potential to result in improved safety and independence among people returning home after stroke.
